## Abstract

**Background:**

Alcohol Use Disorder is a severe mental disorder affecting the individuals concerned, their family and friends and society as a whole. Despite its high prevalence, novel treatment options remain rather limited. Two innovative interventions used for treating severe disorders are the use of real-time functional magnetic resonance imaging neurofeedback that targets brain regions related to the disorder, and mindfulness-based treatments. In the context of the TRR SFB 265 C04 “Mindfulness-based relapse prevention as an addition to rtfMRI NFB intervention for patients with Alcohol Use Disorder (MiND)” study, both interventions will be combined to a state-of-the art intervention that will use mindfulness-based relapse prevention to improve the efficacy of a real-time neurofeedback intervention targeting the ventral striatum, which is a brain region centrally involved in cue-reactivity to alcohol-related stimuli.

**Methods/design:**

After inclusion, *N* = 88 patients will be randomly assigned to one of four groups. Two of those groups will receive mindfulness-based relapse prevention. All groups will receive two fMRI sessions and three real-time neurofeedback sessions in a double-blind manner and will regulate either the ventral striatum or the auditory cortex as a control region. Two groups will additionally receive five sessions of mindfulness-based relapse prevention prior to the neurofeedback intervention. After the last fMRI session, the participants will be followed-up monthly for a period of 3 months for an assessment of the relapse rate and clinical effects of the intervention.

**Discussion:**

The results of this study will give further insights into the efficacy of real-time functional magnetic resonance imaging neurofeedback interventions for the treatment of Alcohol Use Disorder. Additionally, the study will provide further insight on neurobiological changes in the brain caused by the neurofeedback intervention as well as by the mindfulness-based relapse prevention. The outcome might be useful to develop new treatment approaches targeting mechanisms of Alcohol Use Disorder with the goal to reduce relapse rates after discharge from the hospital.

**Trial registration:**

This trial is pre-registered at clinicaltrials.gov (trial identifier: NCT04366505; WHO Universal Trial Number (UTN): U1111–1250-2964). Registered 30 March 2020, published 29 April 2020.

## Background

Alcohol Use Disorder (AUD) is a severe and widespread disease that affects millions of individuals worldwide (World Health Organization (WHO) [54]; Shield et al. [48]). It is characterized by an uncontrollable urge to consume alcohol despite severe psychological or physical health consequences, a loss of social connections, a lack of interests in former joyful activities and an increased tolerance [1]. The consequences not only concern the affected individual but also the social circle (e.g. family, friends, colleagues) and society as a whole [36]. Often, affected individuals are in need of extensive health care and cannot resume their work for many years, which generates high costs for the health care system [3].

Despite the consequences described above, treatment options for AUD are still limited in their efficacy and reach. Only 19.8% of patients with lifetime AUD are ever treated [27] and 45–75% of those relapse 1 year after treatment [6, 30]. To improve this deficient situation, novel treatment options are needed. Optimally, such treatment options would involve the individual patient and support self-efficacy while addressing specific disease-related processes.

A psychologically relevant neurobiological process that is a promising target for such an intervention is cue-reactivity. Cue-reactivity, describing the phenomenon of an elevated response to alcohol-related stimuli, is a frequently disrupted system in AUD patients. Neurobiologically, the elevated response during the presentation of the alcohol related stimuli can be observed in regions such as the anterior cingulate cortex (ACC) and ventral striatum (VS) [46]. Once the brain has habituated to this cue-reactivity, AUD is sustained by the underactivity of prefrontal control regions accompanied by an increased reactivity of the VS [43]. Dysfunctioning of the prefrontal cortical systems [26] including ventromedial prefrontal cortex (vmPFC) [4] and dorsolateral prefrontal cortex (dlPFC) [42] which are regions related to executive functioning moderate the alcohol-seeking motivation, and elicited activation of VS drives alcohol-seeking behavior. This circle maintains repeated alcohol use and relapse after treatment [40, 43, 46].

One of the most applied neuroscientific methods for the investigation of disturbed brain processes in mental disorders is functional magnetic resonance imaging (fMRI), which has provided enormous insights over the last decade. With real-time fMRI neurofeedback (rtfMRI NFB) it is now becoming possible to use fMRI also as an intervention technology. During rtfMRI NFB, the participant is lying in the magnetic resonance imaging (MRI) scanner and the activation of a brain region is measured. A feedback value representing activity of the target region is shown to the participant, while he or she is instructed to find a strategy to regulate the value in a specific direction. So far, rtfMRI NFB has been initially applied in a variety of clinical populations e.g. schizophrenia [13], autism spectrum disorders [10], major depressive disorder [56] and borderline personality disorder [44]. In the field of substance use disorders first studies have used it in nicotine addiction [38], as well as in AUD [14, 35].

While few rtfMRI NFB AUD studies exist, one study has shown that the method has the ability to decrease craving [35]. Furthermore, it was found in non-treatment seeking heavy social drinkers that VS activity can be decreased by means of rtfMRI NFB, which was accompanied by an increase of activity in the right inferior frontal gyrus [39] which is in line with the model of Naqvi & Morgenstern [43].

However, no clinical rtfMRI NFB study has experimentally tested how specific instructions or prior training influence the NFB effect. For example, in our ongoing rtfMRI NFB AUD study [25] patients are not given any instructions about cognitive strategies that might help them control their brain signal prior to the NFB intervention. Nonetheless, studies with healthy participants imply that given said instructions might enhance neurofeedback-based learning [11, 16].

One promising training strategy for rtfMRI in AUD might be mindfulness-based relapse prevention. Mindfulness, which originates in the Pali word “sati” and means being aware, attentive and remembering [5], is defined as “paying attention in a particular way: on purpose, in the present moment, and non-judgmentally” ([32], p. 4). Studies show that mindfulness has many evidence-based benefits, e.g. on the interpersonal, intrapersonal and affective level [2, 15, 33] and might be a useful addition to the therapy of severe disorders [12, 24]. Compared to standard relapse prevention and treatment as usual (TAU), patients receiving the mindfulness-based relapse prevention (MBRP) program showed a significantly decreased risk of relapse to substance use [8, 57].

In order to test whether a prior mindfulness-based training can enhance the therapeutic efficacy that helps the patients regain behavioral control over their alcohol use and learn neural self-regulation with the help of rtfMRI NFB, we therefore combine it here with a mindfulness-based training for addictive behaviors. In the collaborative research center TRR SFB 265 [29] C04 “Mindfulness-based relapse prevention as an addition to rtfMRI NFB intervention for patients with Alcohol Use Disorder (MiND)” study we will assess the influence of MBT on rtfMRI NFB performance and the clinical outcome of the NFB intervention on clinical AUD patients. Insights about potential additional modifiability of VS activity evoked by structured MBRP will be gained in addition to further information about NFB as a state-of-the-art treatment.

## Method

### Hypotheses

We will assess whether intervention success is associated with specific neural correlates and behavioral predictors of variable domains. A prior study has shown that patients who, preceding the intervention, are most responsive to VS cue-reactivity benefit most from the treatment [37]. Therefore, we assume that our study will show similar effects by discriminating between high- and low-responders being premised on their baseline VS cue-reactivity. We expect that the group receiving the combination treatment (real rtfMRI and MBRP) will profit most in terms of the outcome. Considering that relapse will not be defined as an exclusion criterion, we assume a decreased amount of heavy drinking days and a decreased sum of alcohol consumption. Additionally, it is assumed that the number of days until relapse will increase. In contrast to the TAU and sham NFB group, we expect that the other two groups will gain more of an advantage. As a secondary effect, we expect participants with a lower score on alcohol related questionnaires to show a superior long-term outcome in terms of a higher number of non-drinking days.

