### Power calculations

In order to conduct our effect size calculation two studies were used: Hartwell et al. [28], with an effect size of f = .59 in a study focusing on the anterior cingulate cortex in smokers and Kirsch et al. [39], which investigated heavy social drinkers with an effect size of f = .54 for VS cue-reactivity. Additionally, we examined a study by Tang, Tang, & Posner [50] with an effect size of f = .475 on activation in prefrontal control structures after a mindfulness-based intervention. Since the above-mentioned effect sizes originate from small samples, they might be an overestimation of real effect sizes [9]. Thus, we carefully assume an intermediate effect size of f = .3. We conducted the sample size estimation by means of the G*Power software tool version 3 [19]. The region of interest (VS, 200 voxels) was amended for multiple testing based on Bonferroni correction. As a result of this effect size, we require a sample size of 88 participants to attain a significant effect at *p* < .05 (Bonferroni corrected for multiple testing, region of interest mask of 500 voxels) with a power of 80%. With this sample size of 88 participants, we will be able to identify small effects of f = .15 for our primary clinical outcomes with a power of 95% (group by time interaction).

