### Statistical analyses

Offline analyses are conducted with SPM (Wellcome Department of Cognitive Neurology, London, UK) in MATLAB (MathWorks Inc., Sherborn, MA, USA) and include slice-time correction, realignment, segmentation of the anatomical image, normalization to MNI space and smoothing. In our first level analyses, we convolve the time courses with the canonical hemodynamic response function and add them to the General Linear Model (GLM) which also includes 6 movement parameters. The second level analyses comprise correlations with clinical variables and potentially predictive markers for the future course of the disease.

Missing data will be excluded from the analyses. Physiological activity (cardiac and respiratory) will also be recorded and then included in the first level to correct for noise of physiological nature. This will be performed via Global Signal Regression (GSR) and model-based physiology correction [52].

Clinically, the primary outcomes include the number of relapses and the number of days until relapse during the 3-months follow-up. From a neural perspective, the increase of the ability to voluntarily modulate brain activation to alcohol cues after training in the VS serves as a secondary outcome, whereas craving measures such as the Alcohol Abstinence Self-Efficacy Scale [18] will be analyzed as a primary outcome. Another secondary outcome is the influence of combined MBRP and rtfMRI NFB training on functional changes in brain networks of cognitive control (Stop Signal Task (SST), delay discounting).

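### The predictor hypothesis is framed as a high/low contrast on baseline VS cue-reactivity, and no comparison with sham neurofeedback is specified for it

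*Protocol article*

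**What the plan says.** The Hypotheses section of the protocol article starts from a prior study in which patients who "are most responsive to VS cue-reactivity benefit most from the treatment". It expects a similar result here, to be shown by "discriminating between high- and low-responders being premised on their baseline VS cue-reactivity". It gives no cut-point and no model.

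The Statistical analyses section covers markers in one sentence: "The second level analyses comprise correlations with clinical variables and potentially predictive markers". That sentence mentions neither a split nor an interaction with the randomised NFB target.

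The rest of the design bears on this point:

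- Table 1 places the cue-reactivity paradigm at MRI 1 and again at MRI 5, so the selecting measure is re-measured after training.
- The section on sample size and group assignment gives a sham arm (auditory cortex feedback) within both the TAU and the mindfulness groups.
- The Discussion names the comparison of real and sham NFB as an advantage of the study.
- The primary outcomes are relapses, days until relapse and craving measures. Voluntary modulation of the VS is secondary.

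**The concern.** That some patients benefit more from a treatment is a statement about effect modification. It is tested by asking whether the effect of real over sham NFB changes with the baseline marker. Neither a high/low comparison nor a correlation answers that question unless it is contrasted between the randomised arms.

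Two errors are then possible. With a clinical outcome, a marker that predicts the course of the disease under any treatment would be read as predicting benefit from NFB. With change in VS cue-reactivity as the outcome, patients chosen for a high, noisy first measurement will on average fall at the second, and those chosen for a low one will rise, even if NFB does nothing.

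A separate matter is the high/low wording itself. If taken literally, it throws away information from a continuous measure that is scheduled for every patient, and it lets the result depend on where the cut is placed.

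**Working it through.** **The plan's own figure.** The article gives no power for this hypothesis. Its calculation concerns another test: "we require a sample size of 88 participants to attain a significant effect at" the Bonferroni-corrected level, with f = .3, 500 voxels and 80% power. As a 4-group by 2-time interaction with correlation ρ = .5 between the two measurements (the two times and ρ are assumptions):

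- λ = f²·N·m/(1 − ρ) = .09 × 88 × 2/.5 = 31.7, with 3 and 84 degrees of freedom and α = .05/500 = .0001.
- Power is .813. The smallest N for 80% is 87, or 88 for four equal groups.

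So 88 can be reproduced, but it says nothing about the power of a marker test.

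**Loss from a split.** Assume a normal marker cut at quantile q, with c the normal quantile at q. The share of information kept is φ(c)²/[q(1 − q)].

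| Cut | Kept | Lost |
|---|---|---|
| Median | 2/π = .637 | 36% |
| 60th percentile | .622 | 38% |
| 67th percentile | .595 | 41% |
| 75th percentile | .539 | 46% |
| 80th percentile | .490 | 51% |

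- At the median, 88 patients carry the information of 88 × .637 = 56.
- A test with 80% power on the continuous scale (assumed starting point) drops to Φ(2.80 × √.637 − 1.96) = Φ(0.27) = 61%.
- For an assumed true correlation of .3, power falls from 83% to 63% with 88 patients, and from 53% to 36% with 44.

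**Regression to the mean, change in the same VS measure, no treatment effect.** Assume equal variances, retest correlation r and a median split. The mean of the upper half of a standard normal variable is √(2/π) = .798, so the high half falls by (1 − r) × .798 SD and the low half rises by the same amount. The spurious difference is 2(1 − r) × .798.

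The last two columns below come from a null simulation with 3,000 runs and 44 patients per NFB arm (equal allocation assumed). They give the share of runs with a significant result at two-sided p < .05.

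| r (assumed) | Spurious difference | High v low within real NFB only | High v low contrasted with sham |
|---|---|---|---|
| .3 | 1.12 SD | 93% | 4.8% |
| .5 | 0.80 SD | 79% | 5.2% |
| .7 | 0.48 SD | 54% | 5.1% |
| .8 | 0.32 SD | 39% | 4.8% |

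Keeping the marker continuous does not remove this. The correlation of baseline with the fall from baseline is then √[(1 − r)/2] under the null: √.35 = .59, √.25 = .50 and √.15 = .39 for r = .3, .5 and .7.

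**Outcome unrelated to baseline VS.** In the same simulation the within-arm comparison was significant in 4.7% to 5.3% of runs. There is no inflation of this kind for such an outcome.

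**Precision of the interaction.** Take residual SD 1 and a marker with SD 1. A slope pooled over 88 patients has standard error 1/√88. The difference of two slopes from 44 patients each has standard error √(1/44 + 1/44) = 2/√88, which is twice as large. For 80% power at the 5% level the slopes must differ by about 2.80 × 2/√88 = 0.60 residual SD per SD of baseline.

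**The case against.** A reader might infer that the plan commits itself to a median split, discards a third of its information and judges responders without a sham comparison. The document does not support that.

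- The high/low wording is an expectation in the Hypotheses section. It has no cut-point and may be shorthand for a gradient. The correlations named in the Statistical analyses section would keep the continuous scale.
- Nothing restricts the responder analysis to treated patients. The sham arms exist, and comparing real with sham NFB is an announced aim.
- The outcomes that the Hypotheses section goes on to list are clinical (heavy drinking days, amount consumed, days until relapse). The neural outcome is secondary, and it is defined as the ability to modulate the VS, not expressly as change from MRI 1 to MRI 5.
- This is a condensed article, and the model for a predictor analysis is often left to a fuller document.

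All four points stand as limits. The loss from a split and the regression-to-the-mean figures are therefore conditional. What remains is that the methods the article does name for this hypothesis, a high/low contrast and correlations, do not test a claim about benefit from treatment. A general statement that real and sham will be compared does not make the marker analysis an interaction. This rests on what the article says, not on a missing detail.

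**Conclusion.** The point holds in a limited form. As written, the predictor hypothesis is paired with methods that cannot separate prognosis from benefit, although the design contains the arms and the baseline scan needed to do so.

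The size depends on choices the article leaves open:

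- **If the marker is split:** the loss is at least 36% of the information, assuming a normal marker; the median is the best single cut.
- **If the outcome is change in VS cue-reactivity and sham is not used:** chance alone gives a high/low difference of about 0.5 to 1.1 SD at assumed retest correlations of .7 to .3. This does not apply mechanically to relapse or days to relapse, where the risk is mistaking a prognostic marker for a predictive one.
- **If the contrast is made against sham:** the error rate is nominal.

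Normality, the median cut, the 80% starting power, the retest correlations and equal allocation are assumptions, not figures from the document. The primary treatment comparisons are not affected.

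**What to change.** State that the hypothesis will be tested as an interaction between continuous baseline VS cue-reactivity (MRI 1) and NFB target (VS v auditory cortex), with both main effects in the model, in all randomised patients. Use the same term in whatever model suits each outcome. For VS cue-reactivity at MRI 5, the baseline main effect takes up regression to the mean common to both arms, and the interaction is what speaks to benefit. Show high and low responders only in a descriptive plot.

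No extra patients or visits are needed. There are two small costs. Linearity in the marker has to be checked, for instance by plotting. The interaction also has about twice the standard error of a pooled slope, so with 88 patients only a large difference in slopes is likely to be detected. Report it with a confidence interval as a secondary or exploratory result, and do not read a non-significant interaction as evidence that the marker is irrelevant.

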### Sample size, group assignment and recruitment

In order to investigate a possible increased ability of our participants to deliberately reduce VS cue-reactivity through the help of MBRP, we will include *N* = 88 participants. These participants will be recruited from inpatients and outpatients of the clinics of the Department of Addiction Behavior and Addiction Medicine at the Central Institute of Mental Health (CIMH) Mannheim, Germany. After inclusion, they will be randomly assigned to four interventional groups (Fig. 1). While all groups will receive rtfMRI NFB from different brain regions, not all groups will be assigned to take part in the mindfulness-based treatment. Two groups will receive treatment as usual (TAU), whereas the other two groups receive MBRP. These two groups (TAU and MBT) will further each be divided in two subgroups, who receive either rtfMRI NFB from the VS with the instruction to down-regulate it (experimental group) or they receive feedback from the control region which is the auditory cortex (control group). The latter area was chosen since it is unrelated to cue-reactivity.

**Fig. 1 Fig1:**
[figure not shown]
Flow chart. Flow diagram of the study procedure. *N* = 88 AUD participants will be enrolled in the study. They will randomly be assigned to one of four groups, which differ in terms of MBRP and NFB. All groups will be followed-up monthly for 3 months

Participants assigned to the MBT groups will receive five sessions of MBRP in addition to TAU. In the first MBRP session, the patients receive an introduction to mindfulness. Furthermore, patients are taught to observe their thoughts and emotions with an interest but without judging. These sessions include the SOBER-Breathing training [7] which is a form of therapeutic direction using elements of meditation to reduce craving. In the last session, all relevant topics are repeated. Additionally, all participants in the MBRP group will be instructed to practice the shown mindfulness techniques for at least 15 min per day. After completion, the participants will receive the rtfMRI NFB intervention.

The allocation of the NFB technique (target region or control region) is double-blind. Since it is not possible to blind the patients on their additional treatment in form of MBRP, only the staff conducting the MRI scanning session will not be informed about the received treatment (MBRP or TAU) of the participant, which makes this part of the study single-blind.

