### Follow-up assessments

The follow-up assessments are conducted monthly, beginning after the last rtfMRI session. In total, participants are followed-up over a period of 3 months. During the first two follow-ups, participants are contacted via phone and asked whether they use any medication related to alcohol dependence. Additionally, they are inquired about their use of drugs and a possible alcohol relapse. During the last follow-up, which takes place at the CIMH 3 months after the last rtfMRI session, participants are requested to fill out alcohol-related questionnaires and are asked about substance use. For the catamnestic interview, participants are entitled to receive a monetary compensation.

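### Follow-up is dated from the last neurofeedback session, so patients who stop earlier have no relapse assessment scheduled, and the MBRP arms pass one more stage before that point

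*Protocol article*

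**What the plan says.** The protocol article (Method, Sample size, group assignment and recruitment) randomises 88 patients to four groups that cross MBRP or TAU with ventral striatum or auditory cortex feedback. The text below Fig. 1 gives the MBRP groups five sessions and daily practice on top of TAU, and continues: "After completion, the participants will receive the rtfMRI NFB intervention". The abstract gives every group three neurofeedback sessions.

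The section Follow-up assessments states: "The follow-up assessments are conducted monthly, beginning after the last rtfMRI session". The third and last contact falls three months after that session. The abstract counts from the last fMRI session instead, which would be MRI 5 rather than MRI 4. Either way the origin lies after treatment.

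The section Statistical analyses defines the primary clinical outcomes as "the number of relapses and the number of days until relapse during the 3-months follow-up". It also treats craving measures, with the Alcohol Abstinence Self-Efficacy Scale (AASE) as the example, as primary, and it removes missing data from the analyses.

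Table 1 places the Form 90 drinking interview at baseline and its quick version at FU1/2 and FU3, with no drinking interview in between. The AASE is taken at baseline and FU3.

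**The concern.** The window for the relapse outcomes opens at a post-randomisation event that depends on treatment progress, and no other opening date is given. A patient who stops before that event has no date from which FU1 to FU3 can be set. Since nothing in Table 1 records drinking between baseline and FU1, that patient's relapse status is not collected.

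Loss of this kind in every arm would already cost information. The sharper problem is that the two levels of one randomised factor face unequal routes to the same starting point. If the extra MBRP stage leads to extra stopping, and those who stop differ in relapse risk, the MBRP and TAU patients who reach follow-up are no longer comparable by randomisation. An analysis plan written later can choose how to handle missing values, but it cannot recover interviews that were never held.

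**Working it through.** **Step 1. Trace the route to the first relapse assessment.**

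| Stage after randomisation | MBRP arms | TAU arms | Drinking interview |
|---|---|---|---|
| MRI 1 / baseline | yes | yes | Form 90 |
| Five MBRP sessions | yes | no | none |
| MRI 2-4 (neurofeedback) | yes | yes | none |
| FU1-FU3, dated from the last neurofeedback session | yes | yes | Quick Form 90 |

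The three neurofeedback sessions are a condition for follow-up in all arms. The MBRP stage is an additional one in two arms.

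**Step 2. Check whether the sample size allows for loss.** The section Power calculations says "we require a sample size of 88 participants to attain a significant effect", with "we carefully assume an intermediate effect size of f = .3" and "Bonferroni corrected for multiple testing, region of interest mask of 500 voxels) with a power of 80". The test design is not stated. Assuming a group-by-time interaction with 4 groups, 2 measurements and correlation 0.5:

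- alpha = 0.05/500 = 0.0001
- lambda = f² × N × m/(1 − rho) = 0.09 × 88 × 2/0.5 = 31.68, with 3 and 84 degrees of freedom
- required N = 87, or 88 in four equal groups; power at 88 is 81.3%

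So 88 reproduces, and it contains no allowance for loss. (The same section also gives 200 voxels for the region; that would lead to N = 80.) Assuming equal allocation, 44 patients are in the MBRP arms. Losing 10, 20 or 30% of them leaves 40, 35 or 31, a total of 84, 79 or 75. Power in this neural calculation then falls to about 77.5, 71.9 or 66.9%, treating the total as balanced.

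**Step 3. Size of the selection effect with no true MBRP effect.** Let r be the relapse proportion in all randomised patients, d the excess loss in the MBRP arms, and q the relapse proportion among those lost. Loss common to both levels is ignored. None of r, d or q is in the documents, so all are assumed.

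- Relapse in retained MBRP patients = (r − d·q)/(1 − d)
- Spurious difference = r − that value = d(q − r)/(1 − d)

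| r | d | q | Retained MBRP | Spurious difference |
|---|---|---|---|---|
| 0.50 | 0.10 | 0.70 | 0.430/0.90 = 0.478 | 0.022 |
| 0.50 | 0.20 | 0.80 | 0.340/0.80 = 0.425 | 0.075 |
| 0.50 | 0.25 | 0.90 | 0.275/0.75 = 0.367 | 0.133 |
| 0.30 | 0.10 | 0.70 | 0.230/0.90 = 0.256 | 0.044 |
| 0.30 | 0.25 | 0.90 | 0.075/0.75 = 0.100 | 0.200 |

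The last row is an extreme corner: it puts 0.225/0.30 = 75% of all relapses in the arm among the quarter who are lost. A second set of assumptions (r of 30-60%, d of 10-30%, q at 1.3 to 1.6 times r, capped at 95%) gives 1 to 15 points. The sign follows q − r: if those lost relapse less often than average, the bias runs against MBRP.

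**Step 4. Effect on error.** With r = 0.45, d = 0.20 and q = 0.72, retained MBRP patients show (0.45 − 0.144)/0.80 = 0.382, a difference of 6.8 points. With 35 against 44 patients, the chance of a significant result favouring MBRP is about 8.6% instead of 2.5%.

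**The case against.** A reader might infer that the MBRP arms are formally filtered for adherence, so that a patient who leaves MBRP is denied neurofeedback. The text does not support that. The quoted sentence can simply describe order, as the abstract does, and no attendance threshold or withdrawal rule is stated. A patient who misses MBRP sessions but attends neurofeedback has a last session and therefore a follow-up date.

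Three other strong readings also fail:

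- That only the MBRP arms are affected. TAU patients who stop during neurofeedback lack a date too.
- That no primary outcome is collected before follow-up. The AASE has a baseline value. If craving measures are read broadly, the visual analogue craving ratings at MRI 2-4 would also count for patients who get that far.
- That the bias must favour MBRP. This depends on who stops, which the article does not say.

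The article also shows an intent to follow everyone. The Fig. 1 caption has all groups followed monthly for three months, and the Hypotheses section says relapse does not exclude a patient. Finally, follow-up of discontinued patients may be set out in a full protocol that is not shown.

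These points narrow the concern but do not remove it. It needs no attendance rule: anyone who stops before the last neurofeedback session, for any reason, has no start date under the stated schedule. The stated anchor does not deliver the intent to follow everyone. The point concerns a stated anchor, a stated outcome window and a stated exclusion of missing data, not a detail left out for brevity.

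**Conclusion.** The point holds in a limited form. Under the stated schedule, patients in any arm who stop before the last neurofeedback session contribute neither relapse outcome nor a post-baseline AASE value, and they drop out of the analysis. Because the MBRP arms reach that session through one more stage, the MBRP-versus-TAU comparison is open to differential loss. The comparison of feedback regions has no such built-in imbalance.

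The size and direction of any bias cannot be derived from the documents. The figure of about 2-13 percentage points at 50% relapse rests wholly on assumed rates: no true effect, 10-25% excess loss, and 70-90% relapse among those lost. It shows that a moderate imbalance could matter with about 44 patients per level. It does not predict that one will occur. The change is worth making because it concerns data collection, which later analysis cannot replace.

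**What to change.** Date the three follow-up contacts for every randomised patient so that they do not depend on completing MBRP or neurofeedback. Two options are to count from randomisation or from the planned date of the last session. State which is used, because the MBRP stage means that time since randomisation and time since the end of treatment cannot both be equal across arms unless TAU patients wait. Collect Form 90 at each contact, analyse patients in the arm to which they were randomised, and report by arm how many stopped before MRI 2 and how many before the last neurofeedback session.

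Treatment delivery does not change. The cost is protocol wording plus two telephone calls and one visit of an existing type per non-completer. At 10-25% excess loss among an assumed 44 MBRP patients (about 4 to 11 people), that is 8 to 22 calls and 4 to 11 visits, plus the same for patients in any arm who stop during neurofeedback. Including non-completers will slightly dilute the estimated effect, which is the price of keeping the randomised comparison.
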